### Objectives

This paper describes the protocol of a pragmatic randomized controlled trial (RCT), PAC-WOMAN, targeting Portuguese post-menopausal women diagnosed with hormone-receptor-positive breast cancer, currently on Aromatase Inhibitors. This project primary aims are:a) To develop and test the long-term (16-month) effectiveness and cost-effectiveness of two 4-month group-based interventions, compared to a control waiting list, on promoting sustained changes in PA, sedentary behavior, QoL, and healthcare services’ use (primary outcomes)b) To compare the effects of both interventions (i.e., brief PA counseling vs. structured exercise) on long-term changes in our primary outcomes, as well as their cost-effectivenessc) Evaluate pretreatment moderators of 4-month and 16-month changes in PA, sedentary behavior, and QoLd) Identify critical motivational (theoretical) mechanisms of change in PA, sedentary behavior, and QoL, and explore their mediating role.

As secondary aims, we will study the impact of both interventions on AI therapy continuation, adverse events of treatment, disease-free survival, body composition, sleep quality, physical parameters (e.g., muscular strength), and psychosocial factors (e.g., body image). Furthermore, process evaluation will also be conducted seeking to analyze implementation facilitators and barriers.

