In sum, existing interventions targeting supervised exercise, although very effective in promoting short-term health outcomes [43], may be labor intensive and costly for staff and participants. Also, long term effects, once the intervention is finished, may be jeopardized given that supervised interventions may have the detrimental effect of patients’ internalization of the message that their condition is to be dealt with by procedures and techniques essentially under the responsibility and “steering” of an external expert (e.g., simply follow an exercise prescription), thus promoting an external locus of causality. In contrast, theory-based, evidence-informed brief counseling, delivered in a manner that reduces dependence on staff and facilitates self-regulatory skills, could alleviate time and financial barriers while promoting free-living, integrated into daily-life, PA/exercise. From a self-determination theory (SDT) perspective [28], lasting behavior change does not depend on complying with external demands for change but rather on accepting the regulation of change as one’s own. This requires internalizing the regulation of relevant behaviors and integrating them with one’s sense of self and one’s values and goals, so they can become the basis of autonomous regulation [27].

Thus, the PAC-WOMAN trial will test effectiveness and cost-effectiveness of these 2 types of interventions (supervised structured exercise vs. brief theory-based PA counseling) against a waiting-list, standard care, control group. This is of importance given that although an improved health profile (e.g., lower blood pressure, lower body mass index, improved tumoral biomarkers, cardiorespiratory fitness, physical function) is expected as a short-term result of the exercise intervention, the maintenance of the PA/exercise habits after the end of the intervention remains to be determined (and consequently its long-term health outcomes). On the other hand, will a brief motivational (SDT-based) intervention (lighter in time and resources) be enough to trigger a more physically active lifestyle? And will the potential behavioral, motivational, and self-regulatory changes endure in the long term? (With a sufficient magnitude to produce positive health outcomes?).

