#### Interventions

The brief PA counseling (PAC) program will comprise 8 sessions (120 min each), every fifteen days, addressing the following themes: reasons to change, an introduction to the PAC-WOMAN program and principles, types of physical activity and their benefits, strategies on how to become more active and less sedentary, how to safely practice exercise at home, the importance of social support for doing more physical activity, barriers and facilitators for becoming more active, development of coping plans and strategies to overcome those barriers, establishing SMART goals, self-monitoring, medical aspects related to symptom management in breast cancer survivors, body image and self-acceptance, sharing experiences with role models, and re-evaluating action plans.

To increase the potential for long-term behavior change, it is important to target theoretically proposed mechanisms of change and incorporate evidence-based behavior change strategies. Self-Determination Theory (see Rationale for the PAC-WOMAN trial), and several evidence-based behavior change techniques, will be used throughout the intervention. The goal will be to empower participants to develop self-regulation resources, fueled by autonomous motivation to integrate physical activity into daily lives, even in the face of adversity, and thus sustain changes in physical lifestyle. The basic psychological needs of autonomy, competence, and relatedness [28] will be supported in all sessions and intervention materials. More specific SDT-based behavior change strategies will include the provision of choice, meaningful rationale, connection between participants’ health behavior and deep inner values, goal setting, action planning, self-monitoring, coping planning, weighing pros and cons of change in the context of held values and life priorities. Group-based sessions will allow the exchange of experiences, feelings, difficulties, and effective solutions to overcome them, in a respectful, non-judgmental, and supportive environment. The portfolio of strategies, and intervention motivational climate, is in accordance with systematic reviews in this regard [41]. Exercise professionals, previously trained in brief counseling skills for health behavior change and its implementation, will deliver the sessions.

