**Secondary outcomes—Psychosocial Measures**				
Perceived intervention climate	-	X	-	-
Exercise motivational regulations	X	X	X	X
Exercise needs satisfaction/frustration in exercise	X	X	X	X
Affective response to exercise	X	X	X	X
Exercise self-efficacy	X	X	X	X
Self-regulation skills	**-**	X	X	X
Subjective Pain	X	X	X	X
Sleep quality	X	X	X	X
Body image	X	X	X	X
Depressive symptoms	X	X	X	X
Psychological well-being	X	X	X	X

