##### Secondary outcomes: Psychosocial Measures

Perceived intervention climate. Participants’ perception of the facilitators interpersonal behaviors is measured with the Interpersonal Behaviors Questionnaire (IBQ) [76], a 24-item instrument including three support subscales—perceived autonomy, competence, and relatedness support – and three thwarting subscales – perceived autonomy, competence, and relatedness thwarting. Responses are given on a 7-point Likert scale, ranging from 1 (“do not agree at all”) to 7 (“completely agree”).

Exercise motivational regulations. The 24-item Behavioral Regulation in Exercise Questionnaire-3 (BREQ-3) [77] will be used to measure the six forms of motivation proposed by self-determination theory – amotivation, external regulation, introjected regulation, identified regulation, integrated regulation, and intrinsic motivation. Responses are given on a 5-point Likert scale, ranging from 1 (“Strongly Disagree) to 4 (“Strongly Agree”).

Exercise needs satisfaction/frustration. The 24-item Basic Psychological Need Satisfaction and Frustration Scale (BPNSFS) [78] will be used to assess satisfaction/frustration of the three basic psychological needs (autonomy, competence, and relatedness) for exercise. Responses are given on a 5-point Likert scale, from one (“Totally disagree”) to five (“Totally agree”).

Affective response to exercise. The Feeling Scale (FS) [79, 80], is an 11-point scale ranging from -5 (“Very bad”) to + 5 (“Very good”), which assesses the affective valence of exercise.

Exercise self-efficacy. The 9-item Modified Bandura’s Exercise Self-Efficacy Scale will be used to measure how certain participants are/were that they would practice exercise under different conditions or restrictions [81]. Responses are given on a 4-point Likert scale, from 1 (“Very sure”) to 4 (“Not at all sure”).

Self-regulation skills. Action planning (i.e., when, where, what to do, and how often exercise) and coping planning (i.e., how to cope with setbacks and what to do to act according to one’s intentions to exercise) will be assessed the Action Planning and the Coping Planning scales, comprising 5 items each [82]. Action control will be measured with 6 items addressing its different facets, (i.e., self-monitoring, awareness of standards, and self-regulatory effort) [83]. All items are answered on a 4-point Likert scale from 1 (“Completely disagree”) to 4 (“Totally agree”).

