#### Statistical methods

Factorial Anovas with repeated measures, adjusting for potential covariates (e.g., primary treatment, length of AI therapy), will be conducted for primary and secondary outcomes. The analysis will be intent-to-treat to include compliance effects in the overall assessment. Last Observation Carried Forward will be used to impute missing values. A per-protocol analysis will also be conducted without participants who do not attend at least 80% of the sessions. Normality plots and Kolmogorov–Smirnov tests will be used to test normality of outcome variables. If substantial departure from normality is found, square root log transformations will be computed. If normality is still not satisfied, non-parametric tests (e.g., Kruskal–Wallis) will be employed. As the experimental design is factorial, multiple comparison adjustments will not be appropriate.

Mediators of change, i.e., mechanisms by which participants change their lifestyle behaviors and QoL (vs. controls), will be explored using structural equation modeling (AMOS 18.0) and multiple mediation analysis (PROCESS macro v. 3.3 for SPSS). Putative candidates will include motivational (e.g., autonomous motivations) and self‐regulatory (e.g., action planning) variables. Mediation is said to occur when the causal effect of an independent variable (X) on a dependent variable (Y) is partially or fully explained by a mediator (M) [93]. Indirect effects will be tested using Preacher and Hayes’ procedures [94]. Bootstrapping with 5000 samples and 95% CI estimates for indirect effects will be calculated and assumed significant (α = 0.05) if the CI does not encompass zero [95, 96]. The ratio of the indirect effects to the total effects (P_*M*_) will be calculated to express the strength of the mediation effects [95]. Moderators, i.e., baseline characteristics that have an interactive effect with the intervention on the outcome(s), will be assessed to better understand individual differences in intervention effects [97, 98]. Moderation effects on primary outcomes will be conducted at intervention or follow-up’s end.

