To the best of our knowledge, PAC-WOMAN is the first study using Self-Determination Theory as a way of promoting the sustained adoption of an active lifestyle among cancer survivors, by offering a person-centered approach that fosters individuals’ sense of autonomy, competence and relatedness and explores meaningful links between PA and patients’ values and life aspirations, at the same time it stimulates the acquisition of validated self-regulatory skills (e.g., self-monitoring, goal setting or action planning). The significance of the PAC-WOMAN study is further supported by its focus on long-term adherence, along with the investigation of motivational mechanisms mediating changes in PA, sedentary behavior, and quality of life and of putative moderators explaining to whom these two interventions might work best. Finally, PAC-WOMAN is the first RCT study testing the long-term effectiveness and cost-effectiveness of a more traditional exercise program vs. a brief theory-based PA motivational counseling (against a control group). This is of importance given that although a larger improvement in health/fitness outcomes is expected as a short-term result of the exercise intervention, the maintenance of PA/exercise habits in the long term remains to be determined. On the other hand, will a brief motivational (SDT-based) intervention, lighter in time and resources, be enough to induce behavioral, motivational, and self-regulatory changes, and trigger a more physically active lifestyle?

This study is expected to have an immediate benefit to enrolled breast cancer survivors, and a direct impact on the improvement of interventions designed to promote adherence to active lifestyle behaviors. Dissemination of project-related interventions into the community, using community resources in close collaboration with the health care service, will provide much-needed cancer survival management tools that empower patients to maintain health-behavior changes for life, in a familiar social (non-medical) environment. If successful, this study will contribute to a decrease in NHS healthcare use, liberating resources for other needs.

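### Self-regulation skills, a named candidate mediator, have no baseline measurement, so change from baseline cannot be estimated and the skill-to-outcome path cannot be adjusted for prior skill

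*Protocol article*

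**What the plan says.** In Table 2, under the psychosocial secondary outcomes, the row "Self-regulation skills" has a dash at T0 and a cross at T1, T2 and T3. Motivational regulations, need satisfaction/frustration, affective response and self-efficacy all have a cross at T0. The only other psychosocial row without T0 is perceived intervention climate, which cannot exist before an intervention.

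The section on psychosocial measures describes the instruments: five items on action planning, five on coping planning, and for the third scale "Action control will be measured with 6 items addressing its different facets". It gives no reason for leaving out baseline.

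Other sections give this construct a role:
- Objectives, primary aim (d): "Identify critical motivational (theoretical) mechanisms of change in PA, sedentary behavior, and QoL, and explore their mediating role".
- Statistical methods: "Mediators of change, i.e., mechanisms by which participants change their lifestyle behaviors and QoL (vs. controls") are to be explored, and the candidates include self-"regulatory (e.g., action planning) variables".
- Interventions, on the counselling arm: "The goal will be to empower participants to develop self-regulation resources, fueled by autonomous motivation".
- Rationale: "And will the potential behavioral, motivational, and self-regulatory changes endure in the long term"?
- Discussion: the programme "stimulates the acquisition of validated self-regulatory skills".

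**The concern.** The trial asks about change in a construct whose starting point it does not record. Two separate questions are affected, to different degrees.

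The first is whether the programmes raise self-regulation skill. Randomisation takes care of bias here, but a baseline value would sharpen the comparison and is the only route to change within a woman.

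The second is whether skill carries the effect on activity or quality of life. Randomisation does not protect that step. A woman who already plans and monitors her exercise well may both score high at month 4 and be more active for other reasons linked to that earlier skill. Without a T0 score, the mediation model cannot separate this from an effect of skill gained in the trial. The motivational mediators do not have this gap, so the two families of mediators named in the plan cannot be compared on equal terms.

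**Working it through.** **1. Can the items be asked at baseline?** Table 2 restricts only the process evaluation to the intervention groups. The self-regulation row therefore covers waiting-list women, who answer the items at T1 to T3 without having had a programme. Nothing in the article suggests they could not be asked at T0. Items: 5 + 5 + 6 = 16.

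**2. The plan's own figure.** The sample was raised by 25% for mediator and moderator analyses: 98 × 1.25 = 122.5, stated as 122. Mediation therefore helped to set the trial's size.

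**3. Effect of arm on skill.** Assumed: 122/3, or about 41 per arm (equal allocation; no ratio is stated), within-arm SD 1, and T0–T1 skill correlation r of 0.3 to 0.7.
- Standard error without T0: √(2/41) = 0.22. With T0: √[(2/41)(1 − r²)] = 0.21 at r = 0.3 and 0.16 at r = 0.7.
- In simulation, a true difference of 0.50 was recovered with and without T0. There is no bias, only less precision.
- After 25% dropout, about 30 per arm: the difference detectable with 80% power is 0.73 SD without T0, and 0.70 to 0.52 SD with it.

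**4. Effect of skill on activity.** The article gives none of these quantities, so all are assumed and standardised. Arm raises T1 skill by a = 0.5. T1 skill affects T1 activity by b. Baseline skill affects T1 activity directly by s. Baseline skill and baseline activity correlate at q, set equal to s. Baseline activity carries over to T1 activity at 0.4.
- No baseline adjustment: estimated indirect effect = a[b + r(s + 0.4s)].
- Adjusted for baseline activity only: a[b + s·r(1 − q²)/(1 − q²r²)].
- Adjusted for T0 skill as well: a·b, the true value.

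With b = 0 (true indirect effect 0):

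| s | r | No adjustment | Baseline activity only | Plus T0 skill |
|---|---|---|---|---|
| 0 | any | 0 | 0 | 0 |
| 0.2 | 0.3 | 0.5 × 0.3 × 0.28 = 0.04 | 0.5 × 0.06 × 0.96/0.9964 = 0.03 | 0 |
| 0.4 | 0.7 | 0.5 × 0.7 × 0.56 = 0.20 | 0.5 × 0.28 × 0.84/0.9216 = 0.13 | 0 |

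With b = 0.3 the truth is 0.5 × 0.3 = 0.15. Adjusting for baseline activity only gives 0.15 + 0.03 = 0.18 to 0.15 + 0.13 = 0.28, about 20% to 90% too large. Simulation with 41 women per arm gave the same ranges, and returned the true value in every setting once T0 skill was included.

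**5. Imputation.** The plan carries the last observation forward. For this measure, a woman who misses T1 has no earlier value to carry.

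**6. Who can still be measured.** Trial status reports 68 randomised by 27 April 2023: 122 − 68 = 54, and 54/122 = 44%. Over three equal arms that is 18 each, and 18 × 0.75 = 13.5 after the planned dropout.

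**The case against.** Several points can fairly be made in the plan's defence.

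*Acquisition of skill can still be shown.* A reader might infer from the missing T0 that it cannot. The documents do not support that: allocation follows baseline assessment and is random, so the T1 difference from the waiting list is an unbiased estimate of the effect on skill. This stands.

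*A sustained gain would not be hidden.* A reader might also infer that a repeated-measures ANOVA over T1 to T3 would miss a skill gained by month 4 and kept, because the group-by-time term would be null. The Statistical methods section does not single out that term, and the group main effect detects such a gain. With 30 per arm and a 0.5 SD gain, the standard error of the three-visit mean difference is √[(2/30)(1 + 2ρ)/3]. Power is about 0.74, 0.65 and 0.57 for between-visit correlations ρ of 0.3, 0.5 and 0.7. This stands.

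*Confounding is possible, not demonstrated.* Its size rests on correlations the article does not give. T0 activity, self-efficacy and motivational regulations can absorb part of it. A separate simulation of 60 women, adjusted for baseline activity (correlated 0.2 to 0.4 with skill, effect 0.5 on later activity), gave a spurious indirect effect of 0.02 to 0.05. That compares with a sampling SD of about 0.07 and false-positive rates of 2% to 6%. So the bias may be modest next to noise. It is not removed, however, and without T0 the trial cannot tell which case applies.

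*Mediation is exploratory and aim (d) speaks of motivational mechanisms,* all of which have T0. That limits the weight of the point, but the Statistical methods section does list self-regulatory variables, so they are within scope.

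*The remedy comes late.* About 13 women per arm with T0 data cannot support a firm mediation result. This stands, and is why the fix is offered only as a cheap improvement.

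**Conclusion.** The stated schedule works against one of the trial's own questions. Without T0, within-person change in self-regulation cannot be estimated, the arm comparison loses precision (detectable difference 0.73 SD against 0.70 to 0.52 SD), and the skill-to-outcome path cannot be adjusted for prior skill. If prior skill has a direct effect of 0.2 to 0.4 on later activity, and T0–T1 skill correlations are 0.3 to 0.7, a true indirect effect of 0 is estimated at about 0.03 to 0.13 after adjusting for baseline activity. If prior skill has no effect of its own, the bias is zero. These inputs are assumptions, not figures from the article.

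The point concerns one family of candidate mediators. It does not touch the arm comparisons on physical activity, sedentary behaviour or quality of life.

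**What to change.** - In Table 2, change the T0 entry for self-regulation skills from a dash to a cross, using the same 16 items, for every woman not yet assessed at baseline. Use T0 skill as a covariate in the mediation models where it is available.
- For women already randomised, take the between-arm difference (the group main effect over T1 to T3, or the difference at each visit) as the effect on skill, not the group-by-time term. Adjust the skill-to-outcome path for T0 activity, self-efficacy and motivational regulations.
- Report the self-regulation mediation result as open to residual confounding by prior skill.

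The cost is a few minutes of each woman's time at a visit that already takes place, and two versions of the baseline battery within one trial. T0 data would exist for at most 54 of 122 women (44%) at the April 2023 count, so the T0-adjusted subset will have low power. If baseline assessments have since been completed, only the second and third steps apply; they need no new data.

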**Potential covariates**				
Treatment-related factors and demographics	X	-	-	-
AI Therapy length/continuation	X	X	X	X
Food intake	X	X	-	X
**Process evaluation (intervention groups-only)**				
Participants focus groups	-	X	-	X

^a^Assessment performed 6 months after intervention’s start

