#### Study design and setting

PAC-WOMAN is a three-arm, superiority parallel-group, pragmatic randomized controlled trial (RCT), comprising a 4-month intervention period and a 12-month follow-up, that will be conducted to evaluate the effectiveness of two interventions aimed at promoting active lifestyles and improved quality of life in the long-term, albeit with different approaches (brief PA counseling vs. supervised structured exercise), compared to a control group.

Clinical trials can be conceptualized across a continuum from explanatory to pragmatic, with the former assessing if a program could work under ideal circumstances and the latter determining if it could work in real world conditions. Pragmatic trials are necessary for developing and testing interventions using the settings, resources, patients, and approaches to which they will ultimately be implemented [51, 52], thus ensuring that research funds have the greatest potential to impact patient and population health and have therefore been recommended [53].

This project will be conducted under real world circumstances at a main urban center served by several hospitals. Interventions were designed to take place at local gyms, with facilitated accessibility and appropriate equipment and facilities. Recruitment of participants is taking place via dissemination of the trial in main hospitals with oncology centers. A schematic description of the study phases and participant’s timeline, according to SPIRIT, is presented in Table 1. Participants will be enrolled in cohorts or “waves”. Ethics approval was obtained prior to study development/implementation from the faculty responsible for the study (FEFD: M25C21) and all recruitment hospitals (CAML: 285/21; HFF: 10/2022; IPOLFG: UIC/1499; CHLO: 2281). The trial is being conducted in accordance to the declaration of Helsinki for human studies from the World Medical Association [54].

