Quality of life. The European Organization for Research and Treatment of Cancer Quality of Life Questionnaire Core 30 (EORTC QLQ-C30) and its breast cancer module (EORTC QLQ-BR23) are used to measure changes in participants’ quality of life throughout the intervention and follow-up phases, and have previously demonstrated adequate reliability [65, 66]. EORTC QLQ-C30 comprises 30 items, organized in 8 multi-item functional (physical, role, emotional, cognitive, and social) and symptom (fatigue, pain, and nausea) subscales, one global health status and quality of life (QOL) subscale, and 6 single items (dyspnea, insomnia, appetite loss, constipation, diarrhea, and financial difficulties). Breast cancer-related symptoms and side effects are assessed with EORTC QLQ-BR23 module, comprising 23 items, organized in 5 subscales (i.e., body image, sexual functioning, systemic therapy side effects, breast symptoms, and arm symptoms). Five items specifically related to joint, bone, and muscle pain/discomfort, derived from the new EORTC QLQ-BR45 [67], were added provided the specificity of aromatase inhibitors’ side effects.

Healthcare use. Data is collected on healthcare resources use during the study period, namely number and type of consultations, drugs, medical tests and exams, in-patient stays, and day care sessions. Absenteeism is assessed using participants’ reports of their number of absence days or percentage of normal working hours worked, valued at patients’ hourly wage. These resources will then be valued using usual official sources.

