A cost-effectiveness analysis will be conducted, from the NHS and societal perspectives, in comparison with the “no intervention” arm. The time horizon of the study will coincide with that of the intervention follow-up, so that no specific modeling tools will be used. Quality-adjusted life years (QALYs) will be estimated using EORTC QLQ-C30 collected during the intervention, mapped to EQ-5D using mapping algorithms from the literature [97]. Intervention costs will be estimated using a bottom-up approach [99]. Attendance to PA counseling and exercise sessions will be registered; exercise physiologists’ time-related costs will be estimated using their gross hourly salaries, and equipment and disposables’ costs through invoices. Healthcare resources will include consultations, drugs, tests and exams, in-patient stays and day care sessions, valued using usual official tariffs. Absenteeism will be assessed using participants’ reports of their number of absence days or percentage of normal working hours worked, valued at patients’ hourly wage. The incremental cost-effectiveness ratio (ICER) will be calculated as the difference in costs divided by the difference in QALYs between intervention and control groups.

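### Healthcare use, a primary outcome and a cost input to the ICER, is scheduled once, at month 6, which conflicts with the 16-month aim and the stated economic horizon

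*Protocol article*

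**What the plan says.** The Objectives section seeks the "long-term (16-month) effectiveness and cost-effectiveness of two 4-month group-based interventions", compared with a waiting list, "on promoting sustained changes in PA, sedentary behavior, QoL, and healthcare services’ use (primary outcomes"). Healthcare use is therefore a primary outcome, stated as a sustained change. Study design and setting confirms the length of the trial, "comprising a 4-month intervention period and a 12-month follow-up".

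Table 2 lists healthcare use among the primary outcomes, with dashes at T0, T2 and T3 and one mark in the 4-month column. The footnote to that mark reads "Assessment performed 6 months after intervention", counted from its start. Month 6 is none of the four assessment points (0, 4, 10 and 16 months). Every other primary-outcome row is marked at all four.

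The Healthcare use paragraph under Primary outcomes says "Data is collected on healthcare resources use during the study period", without time points or a recall window. Absenteeism is described in the same paragraph and has no row of its own in Table 2.

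Statistical methods assigns repeated-measures ANOVA to the primary and secondary outcomes. For the economic evaluation it says: "The time horizon of the study will coincide with that of the intervention follow-up, so that no specific modeling tools will be used". It counts healthcare resources and absenteeism as costs, and adds: "The incremental cost-effectiveness ratio (ICER) will be calculated as the difference in costs divided by the difference in QALYs between intervention and control groups". It also ties the QALYs to QLQ-C30 data gathered while the intervention runs, although Table 2 schedules quality of life through to month 16.

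**The concern.** The schedule for this outcome does not support the aim attached to it. Without a starting value there is no change to estimate, and one observation per woman gives a repeated-measures ANOVA nothing to work on. If the economic analysis follows Table 2, programme costs, which fall in months 0-4, would be set against at most six months of healthcare use and absenteeism, while QLQ-C30 is scheduled for sixteen. With no modelling planned, nothing fills months 6-16.

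That later window matters most for a trial about lasting change. Dissemination plans makes scale-up depend on the interventions proving cost-effective, and the Discussion anticipates lower NHS use if they succeed. Any saving or added use that builds up after the programmes end would fall largely outside the scheduled data.

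A smaller point belongs here. Aim b) is "To compare the effects of both interventions (i.e., brief PA counseling vs. structured exercise) on long-term changes in our primary outcomes" and goes on to include their cost-effectiveness, but Statistical methods describes the ICER only against control.

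**Working it through.** **Inputs.** Intervention of 4 months and follow-up of 12 months (Study design and setting); one healthcare-use assessment, at month 6 (Table 2 and footnote); horizon equal to the follow-up, no modelling (Statistical methods). The recall window is not stated; I assume 1 to 6 months, where 6 is the longest window that stays inside the trial period.

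**Horizon.** 4 + 12 = 16 months, which reproduces the figure in the Objectives.

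**Coverage** = recall window / 16:

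| Assumed recall (months) | Covered | Not covered |
|---|---|---|
| 6 | 6/16 = 37.5% | 10 months, 62.5% |
| 3 | 3/16 = 18.75% | 13 months, 81.25% |
| 1 | 1/16 = 6.25% | 15 months, 93.75% |

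If the horizon means only the 12 months after the intervention (months 4-16), coverage is at most 2/12 = 16.7%.

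**What month-6 data cannot distinguish.** Let the arms differ by 1 cost unit per month in months 0-6 and by d units per month afterwards (assumed). The 16-month total is 6 + 10d:

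- d = 0: 6
- d = 0.5: 11
- d = 1: 16
- d = 1.5: 21

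The month-6 data are identical in all four cases.

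**Effect on the ICER.** Assume a programme cost of 300 per woman and a constant monthly offset s over 16 months. The QALY difference is held the same in both ICERs, so it cancels, and the ratio of the ICER as measured to the true one is (300 − 6s)/(300 − 16s):

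- s = 0: 300/300 = 1.0
- s = 5: (300 − 30)/(300 − 80) = 270/220 = 1.23
- s = 15: (300 − 90)/(300 − 240) = 210/60 = 3.5
- s = −5 (the intervention raises use): (300 + 30)/(300 + 80) = 330/380 = 0.87

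If an offset exists but stops at month 6, the ratio is 1.0 again. None of these cost figures comes from the document; they show sensitivity only.

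**Change from baseline.** There are no baseline measurements in Table 2, so within-person change cannot be formed.

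**The case against.** The best reply is that the text may describe wider collection than the table. The Healthcare use paragraph speaks of the study period and names no source for resource use; only absenteeism is said to come from participants' reports. Hospital records or continuous logging are not excluded. This stands, and it limits the claim: a reader might infer that ten months of data are certainly lost, but that follows only if Table 2 prevails over the paragraph. It does not remove the problem, because Table 2 positively marks three time points as not assessed. Nor is this detail that an article leaves to a fuller document: the stated schedule conflicts with the stated aim.

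Second, resource use accumulates after randomisation, so a comparison between arms needs no baseline. This also stands. A reader might infer that the outcome cannot be analysed at all; in fact, the level of use over months 0-6 can be compared by arm, to the extent that the recall window reaches back to the start.

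Third, a reader might take the ICER to be systematically wrong, or 3.5 times too high. The document supports neither. The factor of 3.5 comes from one assumed scenario in which the offset nearly cancels the programme cost, and there is no bias if the arms do not differ after month 6.

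Fourth, the QALY window is itself unclear, since Statistical methods points to the intervention period and Table 2 to month 16. The mismatch of 16-month QALYs with 6-month costs therefore follows Table 2 and is not beyond dispute. The narrower reading would bring its own conflict with the 16-month aim.

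Finally, the missing comparison of PAC with StEx is secondary: both arms' costs and QALYs are collected, so it needs no new data.

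**Conclusion.** The concern holds as a conflict between Table 2 and the Objectives, the Healthcare use paragraph and Statistical methods. From the scheduled assessments, at most 37.5% of the 16-month horizon is covered for resource use and, assuming it shares that schedule, for absenteeism. A recall window shorter than 6 months would lower this. Change from baseline, the repeated-measures ANOVA for this outcome and the 16-month cost total are out of reach from those assessments. A randomised comparison of use over months 0-6 is not. Intervention costs are captured separately and are unaffected.

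The bias in the ICER depends on how far the arms differ in use during months 6-16. Neither its direction nor its size can be learned from month-6 data. Since a primary outcome and a primary aim are affected, the passages should be reconciled before the economic analysis is fixed.

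**What to change.** Amend Table 2 so that resource use and absenteeism are collected at the existing T1, T2 and T3 visits, each form covering the time since the last collection. This gives 4 + 6 + 6 = 16 months. Recover missed periods at the next visit or from records. Compare cumulative post-randomisation use by arm.

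Add a look-back form at T0 only for women not yet randomised. Trial status reports 68 randomised by 27 April 2023, which is 68/122 = 56% of the target, so a prospective baseline is no longer possible for them. Use baseline use as a covariate only where it was collected.

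State that QALYs use QLQ-C30 from T0 to T3, so that costs and QALYs share one horizon. If later costs cannot be recovered, limit both to month 6 and drop the 16-month cost-effectiveness claim. QLQ-C30 is not measured at month 6, so utility would have to be interpolated between months 4 and 10. Linearly, month 6 lies (6 − 4)/(10 − 4) = one third of the way.

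Report the PAC versus StEx incremental comparison from the same data, because aim b) includes it.

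The cost is one form at visits that already take place, a table amendment and a little more analysis. The downside is some extra burden for participants and longer recall for the early cohorts. Recruitment opened in January 2022, so anyone who started then would have reached month 16 around May 2023. For such women records may be the only source.
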